## Abstract

**Introduction:**

Distal radius fractures are among the most prevalent traumatic injuries worldwide. These injuries are associated with high healthcare-related and socioeconomic costs, mainly resulting from loss of productivity. To optimise recovery and return to work, wrist exercises are recommended. However, adherence to standard exercise regimens is low. Serious games provide a treatment platform for standardised postoperative care, uniting meaningful recovery with entertainment. Also, mobile serious games, for example, smartphone or tablet applications, are able to send practice reminders believed to improve self-efficacy.

**Methods and analysis:**

To test the effectiveness of a mobile serious game for distal radius fracture rehabilitation compared with standard care, a multicentre, randomised controlled clinical trial was designed. Primary outcome will be the Patient-Rated Wrist Evaluation (PRWE) score after 6 weeks of treatment. Secondary outcomes are range of motion, grip strength, pain scores, and self-reported treatment adherence after 2, 6 and 12 weeks of treatment.

Adult patients with any type of closed distal radius fracture are included directly after non-operative or operative fracture treatment. Patients are recruited in the outpatient clinics of four teaching hospitals. The intended sample size is 92 patients, based on the minimal clinically important difference of the PRWE score at 6 weeks, using a superiority model.

Patients are randomised between using the wearable-controlled mobile serious game *ReValidate!* (intervention group) and standard care consisting of unsupervised exercises and a referral for physiotherapy or exercise therapy upon request or recommendation by the treating clinician (control group).

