### Interventions

After randomisation, patients start participation in the trial as soon as their fracture has been qualified as stable or consolidated, and patients are fit to start active exercises as determined by the clinician; this is either directly, or as soon as possible, but within 3–5 days after cast removal or successful operative fixation. Together with specialised hand and wrist physiotherapists and exercise therapists, a standardised protocol for the first 6 weeks—when most progress is to be expected—has been established that is both embedded within the game and explained to patients.^38^ All patients are instructed by their clinician to perform the hand and wrist rehabilitation exercises three to five times per day. In addition, patients receive a simple diary to complete, with instructions to register their frequency and duration of exercises daily, as well as any physical complaints they may have during exercising.

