#### Intervention group

Patients who are randomised to the game group receive a download link via email, together with instructions on how to download and install the game on their own smartphone or tablet (iPad or iPhone, Apple, Cupertino, California, USA). Patients are instructed to strap one motion sensor to the dorsum of the hand and to strap a second one to the proximal forearm (figure 1). If patients are only in the possession of a compatible smartphone, they will receive the Myo gesture control armband (Thalmic Labs, Kitchener, Ontario, Canada). This sensor is worn around the hand, in combination with the patient’s own smartphone strapped around the forearm with the screen upwards and still visible (figure 1). If patients are only in the possession of a compatible tablet, or if they prefer this option over using their smartphone, they receive two Valedo sensors (Hocoma AG, Zurich, Switzerland). Two separate sensors are used since the tablet cannot be strapped to the arm to be used as a motion sensor. Both types of sensors control the exact same game in the same manner, the motions are the same, and gameplay in both types of game controller has been validated extensively, as described previously.^38^ Both types of motion sensors are CE-marked, have been found fit to act as a game controller and are able to monitor wrist ROM. The sensors are connected to the smartphone via Bluetooth. By using two separate motion sensors placed proximally and distally of the wrist joint, isolated wrist motions are used for game control and patients cannot ‘cheat’ by moving the shoulder joint or the fingers. All otherwise necessary instructions are embedded within the game, making the game ‘self-explanatory’. Intervention group patients will practise with the game for 6 weeks, after which they return the motion sensor to the hospital and are encouraged to continue exercising independently.

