### Outcome measurements

Standard demographic information including age, sex, fracture type according to the Arbeitsgemeinschaft für Osteosynthesefragen/Orthopaedic Trauma Association fracture classification,^39^ and the type of treatment is obtained directly after inclusion. Follow-up visits take place at 2, 6, and 12 weeks postoperatively or after cast removal, for operatively or conservatively treated patients, respectively. A timeline of the trial is shown in figure 3. The primary outcome measure, which is the validated Patient-Rated Wrist Evaluation (PRWE) questionnaire is completed by patients at all follow-up visits.^40 41^ The active ROM is measured in degrees using an analogue universal goniometer. ROM and grip strength are measured in both hands, where grip strength is measured in kilograms, using an analogue hand dynamometer (Baseline, Fabrication Enterprises, White Plains, New York, USA). The maximum value of two measurements with 5 min rest in between is used for analysis. All measurements are performed by a clinician blinded to group allocation that has been specifically trained for this trial, and is experienced in taking ROM and strength measurements in daily practice.

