**Figure 3 F3:**
[figure not shown]
Schematic timeline of the study showing the randomisation and follow-up planning, as well as the outcomes measured during each visit. ORIF, open reduction internal fixation; PRWE, Patient-Rated Wrist Evaluation; ROM, range of motion.

Patients in both study arms complete a questionnaire, that was specifically developed for this trial, on their self-efficacy, experiences and perceived effectiveness of their exercise programme. Pain scores on a Visual Analogue Scale are recorded, and patients are asked about the frequency, if any, of visits to a physiotherapist or occupational therapist. In addition, partial or complete return to work, or to normal functioning if patients were currently unemployed, is registered. Patients are reminded by the researcher to fill out their exercise diary at every follow-up visit and are asked to return their completed exercise diary at 6 weeks of follow-up. In the intervention group, the data on exercise frequency and duration, as well as ROM, will also be retrieved from the serious game. The frequency reported by patients in this group will be compared with the data from the game application, which stores all exercise data including frequency, duration and the ROM measured.

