### Data analysis

The primary outcome is the PRWE score at 6 weeks. This outcome is represented as the change in outcome scores from T0 to T2 (delta, T2–T0). An intention-to-treat analysis is performed, and any missing data are imputed. Data will be analysed using a two-sided t-test or the Mann-Whitney U test, depending on normality of the distribution.

For the secondary continuous outcomes (PRWE score at 2 and 12 weeks, ROM, grip strength, pain scores), a repeated measures analysis of variance will be performed, where group assignment (game group vs control group) is the between-subjects factor, and time of visit (baseline, 2, 6 or 12 weeks follow-up) is the within-subjects factor. In case of a non-normal distribution, generalised estimating equations will be used. An intention-to-treat analysis will be performed, and any missing data will be imputed using multiple imputation. Other (secondary) functional outcomes are analysed as a percentage of the unaffected wrist. Bonferroni correction is applied to all secondary outcomes to correct for multiple tests. Therefore, p values of <0.0045 will be considered statistically significant.

Baseline data and secondary outcomes include categorical data such as fracture type and treatment type. These data will be analysed using the Χ^2^ test, and outcomes will be presented as the differences in frequencies. P values of <0.05 are considered statistically significant. Treatment adherence is measured using a self-reported diary. The number of exercise sessions and the total duration of exercising are continuous variables that will undergo quantitative and qualitative synthesis using a two-sided t-test or a Mann-Whitney U test as appropriate.

The diaries that are handed in after the trial period are analysed for the percentage of days the diary is completed and the total estimated time of exercising. In the intervention group, these data are also compared with the total time of exercising as registered within the game. In addition, should not all diaries be completed, the number of diaries handed in after the study period is registered. These data are then analysed using the Χ^2^ test, and outcomes will be presented as the difference in frequencies.

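### Self-reported adherence is a secondary outcome at 12 weeks, but the diary is returned at 6 weeks; the diary and game-log totals may also cover different days

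*Protocol article*

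**What the plan says.** The abstract of the protocol article (Methods and analysis) gives three time points for the outcome: "self-reported treatment adherence after 2, 6 and 12 weeks of treatment". The Data analysis section names one instrument: "Treatment adherence is measured using a self-reported diary". Under Interventions, patients in both arms receive the diary "with instructions to register their frequency and duration of exercises daily".

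Three statements bear on how long the diary runs. Under Outcome measurements, patients "are asked to return their completed exercise diary at 6 weeks of follow-up". The same sentence begins: "Patients are reminded by the researcher to fill out their exercise diary at every follow-up visit". The visit schedule in that section reads: "Follow-up visits take place at 2, 6, and 12 weeks postoperatively or after cast removal". The Data analysis section, for its part, speaks of diaries handed in once the trial or study period is over.

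The objective source is limited to one arm and to six weeks: "Intervention group patients will practise with the game for 6 weeks, after which they return the motion sensor to the hospital".

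For analysis, returned diaries are "analysed for the percentage of days the diary is completed and the total estimated time of exercising". In the intervention group these data are then set against the total exercise time recorded by the game. The section foresees that not all diaries will be complete. The list of study strengths calls the comparison of patient-reported with objectively monitored adherence reliable.

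**The concern.** Higher adherence is the route by which the Introduction expects the game to improve function, so the adherence results will be read as the explanation of whatever the primary outcome shows. Two things stand in the way.

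First, one of the three stated time points has no clear source of data. If the diary stops at week 6, the trial will either report nothing for week 12 or fill the gap with something not specified in advance. If the diary is meant to run to week 12, the hand-in instruction is wrong, and diaries collected at week 6 will be lost to the later period.

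Second, the agreement between self-report and log is to be judged on two totals. When a diary has gaps, its total covers the days the patient wrote something down, while the game's total covers every day on which the game was played. A gap between them can then reflect missed diary days rather than inaccurate reporting, although the comparison is presented as a test of the latter.

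**Working it through.** The plan gives no numerical figure for adherence to reproduce, and the sample size of 92 does not depend on it. The first part is a comparison of statements; the second is an illustration on assumed values.

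**Part 1: is there a source for week 12?**

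| Possible source | Arms | What the article says about its end |
|---|---|---|
| Diary (the named measure) | Both | Returned at 6 weeks (Outcome measurements) |
| Game log | Intervention only | Sensor returned after 6 weeks (Intervention group) |
| Trial-specific questionnaire | Both | Covers self-efficacy, experiences and perceived effectiveness; not described as recording exercise |
| Question on therapist visits | Both | Counts visits, not exercise sessions |

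On the 6-week reading, coverage is 6/12 = 50% of the follow-up period. Weeks 0–2 and 0–6 can both be taken from daily entries; weeks 6–12 cannot.

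Two statements point the other way. A reminder at every visit includes the visit at week 12, when a diary already handed in could not be filled out. The Data analysis wording on hand-in also suits a diary that lasts as long as the trial. The article does not settle which is meant.

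The planned analysis does not resolve it. Sessions and total duration are compared between arms by a t-test or Mann-Whitney U test with no time point attached, and adherence is not among the outcomes listed for the repeated-measures analysis.

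**Part 2: how far can the diary and log totals diverge with accurate entries?**

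Inputs: 42 days (6 weeks × 7). Sessions and minutes are taken at the middle of the prescribed ranges: 4 sessions a day (from three to five) and 12.5 minutes each (from 10–15), so 4 × 12.5 = 50 minutes a day. The completion rates are assumptions; the article gives none. Assume also that every diary entry is exactly right, that all exercise is game play, and that the patient plays as much on blank days as on others.

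Log total = 42 × 50 = 2,100 minutes. Diary total = 2,100 × completion:

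- 90% completion: 1,890 minutes, 10% below the log
- 80% completion: 1,680 minutes, 20% below
- 70% completion: 1,470 minutes, 30% below

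If instead the patient does not play on blank days, the two totals agree and the shortfall is 0%. The possible shortfall therefore runs from 0% up to the share of blank days. Restricted to days with a diary entry, it is 0% in every row, which is the correct answer for accurate entries.

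**The between-arm totals, as illustration only**

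If both arms truly did 42 × 4 = 168 sessions and blank days added nothing to the sum, completion of 80% and 60% would give 134.4 and 100.8 recorded sessions (ratio 1.33). Completion of 90% and 70% would give 151.2 and 117.6 (ratio 1.29). Equal completion gives a ratio of 1. The article states neither that blanks are summed in this way nor that completion will differ by arm.

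**The case against.** A reader might infer more than the article supports, in three ways.

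- *That blank diary days are counted as no exercise.* Nothing says so. The total is described as estimated, the percentage of completed days and the number of returned diaries are analysed in their own right, and multiple imputation is planned for missing data in the secondary continuous outcomes. It is debatable whether that rule reaches adherence, which is handled in a later paragraph. A day-level rule for blanks is in any case a detail that an article may leave to the full protocol or analysis plan.
- *That adherence as a whole cannot be delivered.* It can be for weeks 0–6, the whole period of game use and the period up to the primary endpoint. Both arms have a diary for it, and the intervention arm has the log as well.
- *That there will be no data at week 12.* This is too firm, because the reminders and the hand-in wording leave open a diary that runs longer.

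It can also be said that the abstract attaches its time points loosely to a list of outcomes, and that adherence was never meant to have a 12-week value. That is plausible, but then the abstract needs correcting; the conflict remains either way.

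On diary and log, the defence is that both are recorded in enough detail to be matched by day, and nothing forbids it. That is fair, and it is why the remedy is cheap. But the comparison described is of totals, in a plan that expects incomplete diaries. The diary may also contain exercise outside the game, for example after a physiotherapy referral. How much is unknown, and it would push the difference the other way.

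**Conclusion.** The point stands in two limited parts. First, self-reported adherence at 12 weeks has no clear data source, and the statements about how long the diary runs contradict one another; this affects one of three time points of one secondary outcome. Second, comparing the diary's total time with the game's total time can misstate how well self-report agrees with the log. The possible shortfall is bounded by the share of blank days: 0% to 30% at an assumed 70% completion, and 0% to 10% at 90%. It arises only if patients play on days they leave blank. The ratios of 1.29 and 1.33 between arms are illustrations on assumed completion rates and are not predictions for this trial. The primary outcome and its analysis are unaffected. The correction is worth making because adherence is the hypothesised mechanism and the diary–log comparison is presented as a strength.

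**What to change.** 1. Reconcile the abstract, Outcome measurements and Data analysis in one of two ways. Either restate adherence as weeks 0–2 and 0–6 and drop 12 weeks, or state that the diary continues to 12 weeks in both arms and change the hand-in time to match. Align the reminder and hand-in wording with the choice. The first option costs only wording. The second costs six more weeks of diary keeping per patient, and weeks 6–12 would rest on self-report alone, with no log to check it.

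2. In the intervention arm, compare diary and game log within patient on days with a diary entry, and report diary completion next to the result. This uses data already collected and costs a sentence in the plan and a merge by date.

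3. Optionally, add between-arm sessions and minutes per completed diary day as a sensitivity analysis. It should not replace the main comparison, because it assumes that blank days resemble completed days. If patients leave the diary blank when they have not exercised, it overstates adherence. The log can check that assumption in one arm only.

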**Ethics and dissemination:**

The protocol has been approved by the Medical Ethical Review Board of the Amsterdam University Medical Centres, location Academic Medical Centre in Amsterdam, the Netherlands. Results will be made available to involved healthcare providers, funders, and to the general public including patients via peer-reviewed academic journals and international conferences.

**Trial registration number:**

Dutch Trial Registry (NTR), NL6140, protocol V.2.

Strengths and limitations of this studyThis study is a randomised controlled trial comparing a wearable-controlled mobile serious game for wrist rehabilitation with standard care, the first of its kind, to the authors’ knowledge.The study is sufficiently powered to show a clinically important difference in the outcome measurements of the primary endpoint.By measuring treatment adherence, both subjectively and objectively, a reliable comparison between patient-reported and objectively monitored treatment adherence can be made.The control group receives an accurate representation of the current standard of care.The analysing statistician will be blinded to randomisation group.

## Introduction

Distal radius fractures are among the most frequently occurring traumatic injuries worldwide, occurring in 18% of patients who present to the emergency department after having sustained any fracture.^1–3^ Up to 25% of fractures occurring in paediatric patients and 18% of fractures in the elderly population are distal radius fractures,^1 4^ with an incidence of 30 and 25 per 10 000 person-years for the age groups under 18 and over 65 years old, respectively.^5^ In the age group over 65 years old, the incidence in women is five times higher than that in men.^4 6^ As the general population ages, the incidence of these injuries is increasing.^1 6–9^ Not only are these injuries a burden to patients affected, they also present a significant socioeconomic burden to society. Hand and wrist injuries are expensive mainly due to the loss of productivity. Distal radius fractures form the largest and most expensive group within this population.^10–13^

Distal radius fractures can be treated either operatively or conservatively.^14^ In order to speed up and enhance recovery of mobility and function after initial fracture treatment, patients are often referred for physiotherapy or hand therapy. Yet, currently available scientific literature remains inconclusive on whether supervised physiotherapy or unsupervised exercise programmes should be advocated.^15–18^ There is consensus that starting exercises early is preferred over starting later,^19 20^ and that performing any type of exercise is most likely more effective than performing no exercises.^21^

Similarly, surgical guidelines from various countries state that exercises are most likely beneficial.^22–25^ These guidelines mostly leave it up to the clinician’s preferences whether or not to refer a patient to a physiotherapist, or recommend a referral when patients suffer severe pain or report oedema.^15 22–25^ This may lead to arbitrary rehabilitation regimens differing per region, hospital and even per individual healthcare provider. It is currently unknown what percentage of patients follow up to physiotherapy referrals. When patients are referred for physiotherapy and follow up to this referral, it has been found that only 19%–35% of prescribed exercise regimens are executed completely and correctly.^26^ Treatment adherence is influenced by practical constraints such as time, costs and travel distances.^27^ Patients with a low self-efficacy will also perceive more barriers to treatment adherence in a home-based exercise programme.^28^ Self-efficacy is defined as the belief one can be successful when performing a certain task and is an important contributor to physiotherapy outcomes.^29 30^

In physiotherapy and rehabilitation, so-called ‘serious games’ have been gaining attention for their presumed effects on motivation and functional outcomes.^31–33^ A serious game is defined as any kind of interactive computer application that incorporates gamification principles and serves an educational purpose, or aims to achieve a predefined goal.^34^ Most studies evaluating the effect of serious games in physiotherapy use consumer-based game consoles with an external hardware component, for example, the Nintendo Wii.^35–37^ These types of games enable patients to perform rehabilitation exercises. As a downside, such games require a game console and a monitor to function, limiting patients in their ability to exercise anywhere they want. A systematic review evaluating the use of serious games in rehabilitation of traumatic injuries described only ‘off-the-shelf’ games. No ‘wearable-controlled’ games could be identified.^32^ Wearable sensors combined with easily accessible gaming platforms such as smartphones or tablets allow the user to exercise anytime and anywhere they want, and can decrease barriers to treatment adherence. To the best of our knowledge, there is no previous research on a home-based wearable-controlled serious game for traumatic injuries.

This multicentre, randomised controlled clinical trial aims to evaluate the effects on functional outcomes of a wearable-controlled serious game played on a smartphone or tablet, that is developed specifically for wrist rehabilitation. This is compared with the current standard treatment following distal radius fracture. This study hypothesises that the use of the game may lead to a higher treatment adherence by improving motivation and adding entertainment to exercises, thus increasing self-efficacy. It is therefore hypothesised that patients recovering with use of the game will show a greater improvement in patient-rated functional outcomes compared with standard treatment. Second, this study aims to compare active range of motion (ROM), grip strength, treatment adherence, pain scores and to measure the effects on return to work between the two treatment strategies.

